## Abstract

**Background:**

The Swiss health ministry launched a national quality program ‘QualiCCare’ in 2011 to improve health care for patients with COPD.

The aim of this study is to determine whether participation in the COPD quality initiative (‘QualiCCare’) improves adherence to recommended clinical processes and shows impact on patients’ COPD care and on the impact of COPD on a person's life.

**Methods:**

CAROL is a cluster-randomized controlled trial with randomization on the general practioner (GP) level. Thirty GPs will be randomly assigned to equally sized intervention group or control group.

Each GP will approach consecutively and regardless of the reason for the current consultation, patients aged 45 years or older, with a smoking history of ≥ ten pack-years (PY). Patients with confirmed (by spirometric evaluation) COPD will be included in the study. GPs in the intervention group will receive ‘QualiCCare’ education, which addresses knowledge, decision-making and behavioural aspects as well as delivery of care according to COPD quality indicators and evidence-based key elements. In the control group, no educational intervention will be applied and COPD patients will be treated as usual. The study period is one year.

The primary outcome measure is an aggregated score of relevant clinical processes defining elements in the care of patients with COPD: smoking cessation counseling, influenza vaccination, motivation for physical activity, appropriate pharmacotherapy, patient education and collaborative care. Given a power of 90% and a significance level alpha of 5%, 15 GPs recruiting eight patients each will be necessary in both study arms. With an assumed dropout rate of 20%, 288 patients will need to be included.

**Discussion:**

It is important to develop and implement interventions that add value to COPD care considering quality and efficiency. Care pathways modifying the knowledge and behavior of physicians have the potential for improving care by transferring knowledge to clinical practice.

**Trial registration:**

ClinicalTrials.gov: NCT01921556

## Background

Chronic obstructive pulmonary disease (COPD), an illness with a prevalence of about 10% in the adult Swiss population causes significant burden to patients and the health care system [1-3]. COPD often remains undiagnosed, and if diagnosed, attention is mainly directed towards pharmacologic treatment, in particular treatment of exacerbations [4]. The course of illness and quality of life of patients can be improved by pharmacological and non-pharmacological interventions [5,6]. Besides appropriate pharmacological treatment, smoking cessation, sustaining physical activity, influenza vaccination and empowering patients to recognize and self-manage exacerbations in an early phase define high quality care of patients with COPD. Recently, we reported on gaps in COPD management in Swiss primary care with overuse of inhaled corticosteroids in moderate COPD and too little emphasis on smoking cessation counseling and patient education [7] (Figure 1). Such deficiencies in health care delivery lead to increased morbidity and excessive use of health care resources [8] and disclose the need for quality improvement.

**Figure 1 F1:**
[figure not shown]
Differences in six chronic obstructive pulmonary disease (COPD) key elements between Swiss primary care and published international data.

Studies in various countries have demonstrated that features of successful COPD care programs are the appropriate delivery of medication, planned regular consultations, activation and education of the patients, adequate exacerbation management and collaborative, integrated disease management [9-13]. The successful COPD programs used more or less a framework known as the chronic care model (CCM) [14] for developing and implementing activities to improve primary care for patients with chronic illnesses. The CCM combines delivery system redesign, clinical information systems, decision support, and self-management support within a practice, linked with health care organization and community resources beyond the practice. Successful implementation of CCM elements provided evidence for improved COPD care [4,15]. An important assumption of the CCM is that the effect of a number of elements and organizational factors combined is higher than their sum of effects.

In 2011, the Swiss health ministry launched the national quality initiative ‘QualiCCare’ to improve the quality of care for COPD patients. In relation to international data, it focuses on adherence with COPD guideline recommendations and on CCM based actions that emerged to improve the course of COPD by prevention and reduction of exacerbations, and thereby also health care costs [4-6,16,17]. These actions include a more proactive and coordinated COPD team care to provide self-management support, smoking cessation counseling, annual influenza vaccination, motivation for physical activity and pulmonary rehabilitation and appropriate pharmacologic treatment considering severity, symptoms and risk of exacerbations. The central aspect of the ‘QualiCCare’ program is a multifaceted implementation approach. It aims not only to increase knowledge but also internal motivation and decision-making by offering stimuli, resources and written instruments [18-21]. Further it categorizes and delineates specific professional and organizational interventions and comprises a short list of evidence-based practice items into a primary care ‘COPD care bundle’ that should guide and support better performance. So far, experience with care bundles for COPD only exists for discharge in patients hospitalized with COPD exacerbations [22].

In Switzerland, such a multifaceted COPD targeted quality program has not yet been broadly implemented and evaluated. The aim of the study is, therefore, to evaluate the effect of the ‘QualiCCare’ COPD intervention on COPD management in patients with diagnosed COPD in primary care practices in the Canton of Zurich.

### Hypotheses

The ‘QualiCCare’ intervention will improve adherence to suggested ‘good care’ standards in COPD, namely: smoking cessation counseling, influenza vaccination, appropriate pharmacotherapy with less overuse of inhaled steroids and correct inhalation technique, consideration of exacerbations, physical activity, pulmonary rehabilitation and patient education, and care coordination. Improvement in these processes is the first step towards improved clinical outcome measures as health status, and therefore, we also expect over time, a reduced impact of COPD on patients’ lives.

## Methods/Design

We will conduct a cluster-randomized controlled trial (randomization on GP level) with primary care physicians in the Canton of Zurich in the years 2013 and 2014.

### Recruitment and eligibility of primary care physicians

GPs are eligible for participation if they provide care in the routine primary setting (single handed practices and group practices) to unselected patients.

About 300 GPs in the area of Zurich and Winterthur are invited to an information meeting by a formal letter of the Institute of General Practice and Health Services Research of the University of Zurich and the Department of Health of the Canton of Zurich. In this information meeting an overview of the study will be given. The main focus of the first information meeting for all GPs is to present the project and to motivate GPs to take part in the study. Additionally, the project will be presented in several quality circle meetings in doctors’ networks (regions Zurich, Winterthur).

GPs who agree to participate will be randomized, stratified by practice organization (single handed versus group practices). All participating GPs/practice assistants will receive instruction by a pneumologist and a spirometry technician in performing a spirometry. Practices in the intervention group get detailed information on evidence-based COPD management and ‘QualiCCare’ training sessions and instruments, designed to increase knowledge, internal motivation and decision-making and to support incorporation of evidence into their daily work (details described in the intervention section).

The GPs of the control group apply ‘care as usual’ without receiving the ‘QualiCCare’ training and implementation tools.

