### Patient recruitment

All GPs are asked to approach consecutively and regardless of the reason for the current consultation, patients aged 45 years or older with a smoking history of ≥ ten pack-years (PY) and to include patients with COPD diagnosed by spirometric evaluation.

To assure an appropriate spirometric evaluation, all GPs will participate in a spirometric training by a pneumologist and a spirometry technician before starting the patient recruitment process and before randomization of the GPs. The aim of this procedure is to diagnose COPD or confirm the diagnosis of COPD by a current and correct spirometry in both arms of the study.

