### Implementation program

#### Instruction of the GPs and practice assistants in the intervention group

Physicians randomized into the intervention group get a ‘QualiCCare’ training workshop designed to educate professionals on the guidelines, but also and particularly, governing professional behavior by feedback, reminders and pathways that help to change their attitudes and care behavior [23-25]. Based on behavioral and learning theory [26], ‘QualiCCare’ intervention not only tries to increase knowledge but also internal motivation and decision- making by stimuli and resources and by written instruments that guide evidence-based decision support.

The education sessions will actively involve GPs and practice assistants with tasks and responsibilities and also, by demonstrating them (by interactive teaching, case vignettes and role plays), ways on how evidence-based tasks could be incorporated into their daily work.

Three instruments (A-C) have been developed based on a review of international and national guidelines and in collaboration with the Swiss Respiratory Society, Swiss Societies of Internal and General Medicine and College of Primary Care Medicine, with a specific focus on primary care circumstances and needs. These instruments will be introduced to the intervention group as working tools for daily practice to support decision-making and adherence with recommended COPD care.

A. The Swiss COPD quintessence for primary care is a clinical guideline for GPs which is consistent with international guidelines for COPD [27] and the newly published Swiss COPD guideline [6], but more comprehensive and summarizing the key elements of COPD management for Swiss primary care [28].

B. The COPD pocket guide contains evidence-based information, assessment tools (MRC, CAT, STS), opinion sheets (early diagnosis, smoking cessation advice), treatment algorithm and decision aids for the key COPD elements: Confirm diagnosis, Optimize symptoms, Prevent deterioration, and Develop network and self-management support. The pocket guide also contains addresses and links to useful information as well as for specialist support, pulmonary rehabilitation and community resources offering, for example, smoking cessation and patient education.

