C. The Primary care COPD Care bundle is something new for the primary care setting. So far, experience for COPD only exists for discharge care bundles for COPD patients hospitalized with acute exacerbations. The implementation of a discharge care bundle improved adherence with optimum health care practice [22]. Our primary care COPD care bundle comprises a short list of evidence-based practice items to be implemented into primary care for patients with COPD. It can function as a reminder and as a checklist of all necessary activities that can be ticked as performance control. It is expected to function as a stimulus for increased guideline adherence and internal motivation for behavior change.

Bundle items selected for primary care are:

1. Identify COPD in a smoker or ex-smoker (with at least ten PY) with symptoms (cough, sputum or dyspnea).

2. If the patient is still a smoker, offer smoking cessation assistance.

3. Motivate for physical activity and consider/refer for pulmonary rehabilitation.

4. Motivate for influenza vaccination.

5. Offer appropriate pharmacologic treatment for stable and exacerbated COPD.

6. Demonstrate and check correct use of inhalers.

7. Give written information about COPD including Lunge Zürich self-management booklet and an action plan.

8. Offer proactive follow-up and integrated services (for example follow-up, feedback and scheduling and ‘navigation’ functions by the trained practice assistant, arranging appointments, and connecting patients to internal and external providers and resources).

A specialized and experienced team of a pneumologist and a respiratory physiotherapist and master trainer will hold the ‘QualiCCare’ training workshop (half a day session). The three dimensions knowledge, skills and behavior in COPD management are addressed with consideration of the COPD care bundle items.

A ‘QualiCCare’ refresher course will be held six months after the first training workshop.

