### Timeframe of the study

The recruitment of the 30 GPs is planned over two months between July and August 2013 (−T2).

Patient eligibility screening and patient inclusion is projected within a period of three months (−T1). The intervention courses will start subsequently.

Assessments will be made as described above, T0 baseline assessments start from the inclusion; at baseline, data regarding COPD management in the year before inclusion will also be assessed retrospectively from the patient charts and transferred anonymously to the study center.

Final measurements (T1) will be performed one year after the ‘QualiCCare’ intervention.

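### GP-level randomisation with group practices eligible allows one practice to be split between arms, although the intervention works through the practice and its assistants

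*Protocol article*

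**What the plan says.** The unit of randomisation is the GP. The abstract states "CAROL is a cluster-randomized controlled trial with randomization on the general practioner (GP) level", and the opening of Methods/Design repeats it. GPs qualify if they work in the "routine primary setting (single handed practices and group practices" categories, so several GPs of one practice may join. The allocation rule is "GPs who agree to participate will be randomized, stratified by practice organization (single handed versus group practices". Practice type is the stratum; practice identity plays no part. The article neither limits entry to one GP per practice nor allocates colleagues jointly.

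The intervention is described at practice level. The section on recruitment of physicians says that intervention practices receive the information, training and instruments, while it defines the comparator as control GPs who work without the training and tools. In the implementation programme, "The education sessions will actively involve GPs and practice assistants with tasks and responsibilities". The last item of the care bundle assigns follow-up, scheduling and navigation "functions by the trained practice assistant". The outreach visit, described under data collection, examines practice structures and puts solutions in place.

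On timing, the patient recruitment section places spirometry training before both patient recruitment and randomisation. It does not order those two. The timeframe section lists GP recruitment, then three months of patient inclusion, and then: "The intervention courses will start subsequently". It does not place randomisation in that sequence. The flow chart is not shown.

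**The concern.** Stratifying by practice type balances the number of group-practice GPs between arms. It does nothing to keep colleagues together: colleagues always sit in the same stratum, and that stratum is itself divided between the arms.

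If a practice is split, its control GP may share a trained assistant, the checklist, the patient booklet and reorganised follow-up with an intervention colleague. That conflicts with the article's own description of the control condition. The effect is contamination: control patients receive part of the intervention and the difference in the primary score shrinks. A larger sample does not cure this, because the estimate stays diluted even when it is significant.

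The secondary issue is selection. The GP approaches patients, applies exclusions that involve judgement (other severe disease, language skills) and informs them for consent. If the GP knew the arm at that stage, the two arms could recruit different kinds of patient.

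**Working it through.** **Inputs** (Calculation of sample size): difference 1.5, SD 2.3, ICC 0.04, 30 GPs with 8 patients each (240), power 90%, alpha 5% (taken as two-sided). The abstract gives 15 GPs per arm.

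**Step 1. The plan's own figure.** Without clustering, n per arm = 2 × [2.3 × (1.960 + 1.282) / 1.5]² = 49.4. The design effect is 1 + (8 − 1) × 0.04 = 1.28. The product is 63.2, so 64 per arm and 128 in total. The stated 240 is not reproduced. With 240 patients the standard error of the difference is 2.3 × √(2 × 1.28 / 120) = 0.336, the noncentrality is 1.5 / 0.336 = 4.47, and power on 28 df (30 GPs − 2) is 99.1%. The mismatch with 90% is a separate matter. It is noted here because it explains why the figures below start from 99%.

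**Step 2. How easily a practice is split.** With one GP assigned, 15 of the remaining 29 places are in the other arm, so a pair is split with probability 15/29 = 52%. Stratification does not lower this. In an assumed group-practice stratum of 10 GPs divided 5:5, the probability is 5/9 = 56%. With three such pairs, treated as independent, at least one is split with probability 1 − (14/29)³ = 89%.

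**Step 3. What dilution would cost.** GP-level randomisation, 240 patients, standard error 0.336, t-test on 28 df. The share of the effect lost is an assumption.

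| Share lost | Remaining difference | Noncentrality | Power |
|---|---|---|---|
| 0% | 1.50 | 4.47 | 99.1% |
| 20% | 1.20 | 3.57 | 93.2% |
| 30% | 1.05 | 3.13 | 85.5% |
| 50% | 0.75 | 2.23 | 57.8% |

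As a guide to these shares: if an exposed control GP gained the full 1.5, a 20% loss would need 3 of 15 control GPs exposed, and a 50% loss 7 or 8.

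**Step 4. What practice-level randomisation would cost.** 240 patients, an assumed average of g participating GPs per practice, and ICC held at 0.04 for the practice. The design effect is 1 + (8g − 1) × 0.04, with 30/g practices and 30/g − 2 df.

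| g | Practices | Design effect | Power for 1.5 |
|---|---|---|---|
| 1 | 30 | 1.28 | 99.1% |
| 1.5 | 20 | 1.44 | 97.8% |
| 2 | 15 | 1.60 | 95.8% |
| 3 | 10 | 1.92 | 89.0% |

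**Step 5. Timing.** No arithmetic applies. The recruitment section says who is randomised (those who agree). The patient recruitment section says what comes first (spirometry training). The timeframe section says what comes last (the courses). None states whether allocation precedes or follows patient inclusion.

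**The case against.** GP-level randomisation is a declared choice, and nothing in the article says that two GPs of one practice will take part; 30 are sought from about 300 invited. Single-handed GPs have no practice colleague in the other arm, so the upper end of the dilution range needs many split group practices. At 20% dilution power is still above 90%, and the bias runs towards no effect, so it cannot by itself create a false positive. All of this stands and limits the likely size. It does not remove the problem: the plan as written permits split practices, the trial can guard against them cheaply, and a diluted estimate understates the programme's effect whatever the power.

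On timing, a reader might infer that GPs are randomised one by one at the moment they agree, and so know their arm while choosing patients. The documents do not support this. Agreement is the condition for randomisation, not its moment. Spirometry training comes before it, and equal groups of GPs fit a single batch allocation at least as well. The missing flow chart may settle the order. There are also real safeguards: "All GPs are asked to approach consecutively and regardless of the reason for the current consultation" describes the approach in both arms, obstruction must be confirmed by spirometry, both arms get the same spirometry training, and the courses come after inclusion. Baseline data on earlier care would show some imbalance and allow partial adjustment. These safeguards reduce the risk of selection but do not conceal allocation.

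**Conclusion.** The contamination point holds. Randomisation by GP, eligibility of group practices and a practice-based intervention together allow colleagues who share trained staff to fall in opposite arms, at about 52% per participating pair, with a bias towards zero. The size cannot be fixed from the article, because the number of GPs per practice is not given. The fall in power to 93.2%, 85.5% or 57.8% illustrates assumed losses of 20%, 30% or 50% and is not a forecast. It rests on the stated SD and ICC and on a cluster-level test.

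The timing point holds only as an open question: the text shown does not rule out that GPs know their arm during patient selection. It does not show that they do, and a selection effect cannot be sized from it.

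**What to change.** 1. Randomise practices, so that all participating GPs of one practice go to the same arm. Keep the stratification by practice type, and treat the practice as the cluster in the analysis. The cost is fewer independent units. The spare power at 240 patients covers this at an average of 1.5 or 2 GPs per practice (97.8%, 95.8%) but not quite at 3 (89.0%). The expected number of GPs per practice should therefore be stated and the sample size checked against it. Arms of exactly 15 GPs may no longer be attainable.
2. State where randomisation falls relative to patient inclusion, and withhold allocation until inclusion and the T0 questionnaires are complete. The courses already start only after inclusion, so this costs little more than a later notice to the practices. The trial status section reports that patient recruitment had not begun at first submission, so at that stage withholding allocation was still possible.

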### Patient recruitment

All GPs are asked to approach consecutively and regardless of the reason for the current consultation, patients aged 45 years or older with a smoking history of ≥ ten pack-years (PY) and to include patients with COPD diagnosed by spirometric evaluation.

To assure an appropriate spirometric evaluation, all GPs will participate in a spirometric training by a pneumologist and a spirometry technician before starting the patient recruitment process and before randomization of the GPs. The aim of this procedure is to diagnose COPD or confirm the diagnosis of COPD by a current and correct spirometry in both arms of the study.

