### Outcomes

#### Primary outcome

Difference in ‘quality of care process’ (total increase in performed measures/fulfilled indicators) after one year between COPD patients in the intervention and control group as reported by the patient (described below).

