### Data collection procedures

#### Patient questionnaire

The patients will receive detailed written information on the aim of the study. After giving their written informed consent they will receive a questionnaire (T0) assessing gender, age, employment status, and family background, the CAT, information on respiratory symptoms (cough, sputum, dyspnea), and severity of dyspnea (Medical research council MRC dyspnea scale), smoking status, motivation to quit, exacerbations and health care utilization (including unscheduled visits, emergency department attendances and hospital admissions due to pulmonary problems). Patients are asked at T0 whether, in the previous year before study inclusion, they had received: advice to quit smoking, assessment and advice for physical activity or advice/referral to pulmonary rehabilitation, recommendation/application of influenza vaccination, patient education with defining COPD and information about the main causes, signs and symptoms, information on medication and using inhalation devices with face-to-face instruction and demonstration of inhalation technique, information on how to identify and manage an aggravation of symptoms (exacerbation) and an action plan for exacerbation management including medication adjustment for exacerbation treatment. In addition patients are asked whether they have received COPD support by community resources (lung associations, support groups) and other specialized health professionals. Patients are asked the same questions one year after study inclusion T1. They receive the questionnaires and stamped envelopes with the postal address of the university and are asked to return the questionnaire in the envelope to the university at T0, and T1 after 12 months.

Patients will also be informed that neither the GP nor the practice team has any possibility of obtaining knowledge of their answers.

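### The primary increase score mixes known COPD with COPD first found at inclusion, and prior diagnosis is not a listed baseline item; one yes/no question and a covariate would remove the case-mix noise

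*Protocol article*

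**What the plan says.** **Who enters.** Under Patient recruitment, GPs are asked "to approach consecutively and regardless of the reason for the current consultation, patients aged 45 years or older", provided they have enough pack-years. The spirometry serves two purposes: "The aim of this procedure is to diagnose COPD or confirm the diagnosis of COPD by a current and correct spirometry". The inclusion and exclusion criteria require obstruction on spirometry but no earlier diagnosis, so newly found cases are eligible. The Background accepts that such patients exist: "COPD often remains undiagnosed".

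**Stated target.** The last paragraph of the Background gives the aim as the effect on "COPD management in patients with diagnosed COPD in primary care practices in the Canton of Zurich".

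**Outcome.** The Primary outcome section compares the arms on the "total increase in performed measures/fulfilled indicators" after one year, as reported by the patient, on a score from 0 to 9.

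**Look-back.** Under Patient questionnaire: "Patients are asked at T0 whether, in the previous year before study inclusion, they had received" a list of care items. The same questions come again at T1, one year after inclusion.

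**Baseline data.** The lists under Baseline, Patient questionnaire and GPs name demographics, symptoms, spirometry, GOLD grade, drugs, exacerbations and health care use, among others. None names whether COPD had been diagnosed before inclusion. The Timeframe section adds a chart review of COPD management in the year before inclusion.

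**Analysis.** The Data analysis section plans an independent-groups t-test for the primary outcome.

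**The concern.** For a patient whose COPD was already known, the T0 year and the T1 year offer much the same opportunity to receive COPD care. For a patient first diagnosed at inclusion they do not, because nobody had yet applied the label that prompts COPD education and, largely, exacerbation assessment and inhaler instruction. The increase score therefore measures two things at once: a change in care, and a change in diagnostic status.

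How much of the second enters depends on the share of new cases. That share probably varies between GPs with their earlier use of spirometry, and there are only 15 GPs per arm. If it differs between arms, the between-arm difference in increase moves for a reason unrelated to the intervention. Even if it is balanced, it adds spread to the score. An unadjusted t-test removes neither, and without a record of prior diagnosis no later analysis can do so cleanly.

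**Working it through.** **1. The plan's benchmark.** The sample-size section gives an effect of 1.5, SD 2.3, ICC 0.04, 8 patients per GP, 30 GPs, 90% power and 5% alpha.

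- Per arm before clustering: 2 × (2.3 × (1.960 + 1.282) / 1.5)² = 49.4, so 50.
- Design effect: 1 + (8 − 1) × 0.04 = 1.28.
- Per arm: 50 × 1.28 = 64, or 128 in total.

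The stated 240 is not reproduced. That is a separate matter and is used here only as a benchmark: 120 per arm gives 99.4% power if 2.3 is the SD of the analysed score.

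**2. Which indicators depend on the diagnosis.**

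- Indicator 9 (education) clearly does; 6 (exacerbation assessment) and 8 (inhalation technique) probably do.
- Indicators 1 to 5 (smoking, influenza vaccination, physical activity) can be met in any smoker or ex-smoker without a COPD label.
- Indicator 7 runs the other way. An untreated new case with FEV1 > 50% and fewer than two exacerbations takes no inhaled corticosteroid, so it may be met at T0 and can then only stay or fall.

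So K = 3 indicators start at or near the floor. Leaving indicator 7 out makes the figures below, if anything, too high.

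**3. Assumptions.** The article gives no share of new cases and no attainment. I take f, the share newly diagnosed, as 10% to 50%, and q, the excess chance that each of the three items is gained by T1 in a new rather than a known case, as 0.2 to 0.8.

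**4. Rise common to both arms:** K × q × f.

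- Low: 3 × 0.2 × 0.1 = 0.06 points.
- High: 3 × 0.8 × 0.5 = 1.20 points.

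With equal f and q this drops out of the between-arm difference.

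**5. Shift if f differs between arms:** K × q × (difference in f).

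| Difference in f | q = 0.2 | q = 0.5 | q = 0.8 |
|---|---|---|---|
| 10 points | 0.06 | 0.15 | 0.24 |
| 20 points | 0.12 | 0.30 | 0.48 |

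**6. Is a 10 to 20 point difference plausible by chance?** The 95% limit is 1.96 × √(2f(1 − f)/120 × design effect).

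- f = 0.1, design effect 1.28: 1.96 × √0.00192 = 8.6 points.
- f = 0.4, design effect 1.28: 1.96 × √0.00512 = 14 points. This is 0.28 score points if a new case gains 2 items and 0.42 if it gains all 3.
- f = 0.4, assumed ICC 0.20 for new-case share (design effect 2.4): 1.96 × √0.0096 = 19 points, or 0.38 score points with 2 items.

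The ICC of 0.04 is the plan's value for the outcome. Nothing in the article says it applies to the share of new cases.

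**7. Added variance:** f(1 − f)(Kq)².

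- Low: 0.09 × 0.36 = 0.03. High: 0.25 × 5.76 = 1.44.
- SD: √(5.29 + 0.03) = 2.31 to √(5.29 + 1.44) = 2.59.
- Power at 240: 99.4% down to 97.7%.

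The article does not say whether 2.3 is the SD of a score or of a change. For an uncorrelated change the SD would be 2.3 × √2 = 3.25, with 88.4% power at 240. Adding 1.44 gives √(10.58 + 1.44) = 3.47 and z = 1.5 / (3.47 × √(2/93.75)) − 1.96 = 1.00, about 84% power (93.75 = 120/1.28).

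**The case against.** The strongest answer is that the trial is randomized and the primary test is between arms. A reader might infer that the primary result is biased because COPD-specific indicators rise in both arms by construction. The documents do not support that. A common rise cancels, and a floor only means the items cannot fall; whether they rise among controls depends on usual care, which the Background describes as weak on patient education. Nor does the article plan to interpret a within-arm rise, so setting the common rise beside the planned 1.5 compares unlike quantities. This objection stands in full.

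Second, a chance difference in case mix under randomization is sampling error, not bias, and the standard error already allows for it. This stands too: the loss is precision. A systematic difference would need recruitment to depend on allocation. The article is not explicit about whether GPs know their arm while enrolling, but inclusion is placed before the intervention courses and spirometry training is common to both arms. Systematic imbalance is possible but not shown.

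Third, a reader might infer that prior diagnosis is not recorded at all. A condensed article cannot show that, and the chart review may reveal earlier COPD care. This stands in part. Absence of COPD care in the chart does not separate an undiagnosed patient from one diagnosed but not cared for, and the second is the gap the trial addresses.

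Fourth, every included patient has diagnosed COPD once enrolled, so the aim can be squared with the recruitment rule. That reading is available, but the other, that patients were diagnosed beforehand, is equally natural.

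**Conclusion.** The point holds as a cheap improvement, not as a flaw that invalidates the primary comparison. The eligibility rule, the pre-inclusion look-back and the increase endpoint together make the score depend on whether COPD was known before inclusion, and the listed baseline items do not capture that.

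The planned between-arm test is not biased by this alone. The cost is added variance and sensitivity to case mix: a shift of about 0.06 to 0.48 points for a 10 to 20 percentage point difference in new-case share, against a planned 1.5. Loss of power is minor if 2.3 is the SD of the analysed score (97.7% or more at 240) and moderate if the change score is as variable as two uncorrelated measurements (88.4% to about 84% at the extreme). All sizes rest on assumed values: three affected indicators, 10% to 50% new cases, and 0.2 to 0.8 excess attainment per item.

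**What to change.** - Add one yes/no item to the T0 GP form: COPD diagnosed before study inclusion. The Trial status section says recruitment had not started at first submission; the status is harder to reconstruct later.
- Report its distribution by arm.
- Include it as a prespecified covariate in the primary between-arm analysis. The unadjusted t-test then becomes a linear model with arm and prior diagnosis.
- Show the between-arm effect in previously and newly diagnosed patients as a descriptive subgroup display, without a separate claim.
- Reconcile the aim in the Background with the Patient recruitment section, stating whether the target is all spirometry-confirmed COPD or only COPD known beforehand.

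The cost is one form item and one model parameter. The subgroup estimates will be less precise than the overall effect.
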